### Patient groups

#### *Septic shock* (*n* = 60)

Septic shock is defined as sepsis-induced hypotension, characterized by systolic blood pressure < 90 mmHg or a drop of > 40 mmHg from baseline or mean arterial pressure < 65 mmHg, persisting despite adequate fluid resuscitation. Adequate resuscitation will be considered achieved when a volume of at least 30 ml/kg of crystalloids will be administered. Additional fluid resuscitation will be guided using hemodynamic monitoring according to local practices. Subgroup analyses will be undertaken to compare the community-acquired and nosocomial-acquired infections.

#### *Cardiogenic shock* (*n* = 30)

Cardiogenic shock is defined as a state of inadequate circulation of blood because of ventricular failure due to acute cardiac conditions, such as acute myocardial infarction (AMI) or prolonged arrhythmias (PA). Additionally, characteristics of the CS patients recruited in *ShockOmics* will be: hypotension, characterized by systolic blood pressure < 90 mmHg or a drop of > 40 mmHg from baseline or mean arterial pressure < 70 mmHg, persisting despite adequate fluid resuscitation; Cardiac Index <1.8 L/min/m^2^ without supports or < 2.0–2.2 L/min/m^2^ with the support of inotropic drugs (e.g. dobutamine/isoprenaline/phosphodiesterase inhibitors or levosimendan) or of cardiac assistance devices; cardiac overload or altered left/right ventricular function are assessed by typical echocardiographic indices [15]:Left ventricular (LV) volume and ejection fraction (EF) estimated by the apical biplane method of disks (modified Simpson’s rule):EF <35 % = systolic heart failureLV diastolic volume/ body surface area (BSA) > 97 ml/m2 = severe LV dilationAortic velocity time integral (VTI) measured by PW Doppler on LVOT:Abnormal if < 18 cmSeverely abnormal if < 14 cmMitral annular diastolic PW tissular Doppler velocities:Lateral E/E’ >12 = high LV filing pressureE/E’ <8 = normal LV filing pressureRight ventricular /left ventricular (RV/LV) diameter (or cross section area) ratio > 1 = severe RV overload (intermediate if between 0,6 and 1).Paradoxical inter-ventricular septum motion (or “D-shape”) = severe RV overload

#### Hemorrhagic shock (*n* = 15)

Hemorrhagic shock is a hypovolemic form of shock, characterized by the rapid loss of significant amounts of blood, systolic blood pressure < 90 mmHg or a drop of > 40 mmHg from baseline or mean arterial pressure < 65 mmHg. The HS patients enrolled in the study will be analyzed exclusively from the standpoint of their hemodynamic records and clinical data.

#### Control groups (*n* = 30)

The *ShockOmics* study will also entail the collection of blood samples and hemodynamic data when possible in comparison groups of healthy subjects or patients not it shock:*n* = 5 healthy blood donors will be collected for the purposes of obtaining reference values for proteomics analysis*n* = 10 septic patients not in shock: sepsis caused by infections with inflammatory response with one organ dysfunction at most (as indicated by SOFA sub-scores for specific organ function), without organ support therapy (i.e., mechanical ventilation, renal replacement therapy) and with lactate levels < 2 mmol/L*n* = 10 cardiac patient not in shock, affected by AMI or PA patients

### Inclusion and exclusion criteria

The inclusion criteria of *ShockOmics* are:SOFA score > 5First blood sample and first hemodynamic measurements available within 16 h from admission to the ICUInformed Consent available: the consent will be requested to the patient, or to its relatives in case of altered consciousness, and signed by the physicians responsible for *ShockOmics* in the ICU. Delayed consent may be asked according to local rules and regulations in case the relatives were unavailable at the time of potential enrollment

The exclusion criteria of *ShockOmics* are:Risk of fatal illness and death within 24 hPatients already enrolled in other interventional studiesMore than 4 units of red blood cells transfusedPatients receiving plasma or whole bloodActive hematological malignancyMetastatic and/or active cancerImmunodepression, including transplant patients; patients infected by the human immunodeficiency virus (HIV+); constitutive immune system deficiency; any immunosuppressive therapy, including oral and parenteral corticosteroids (aerosols are allowed)Patients with pre-existing end stage renal disease needing renal replacement therapy. The introduction of continuous veno-venous hemofiltration from the day of admission onward is allowedCardiac surgery in the previous ten daysChild-Pugh C cirrhosis or acute liver failureTerminal illness

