In the context of low blood pressure, low flow, and reduced ventricular contractility typical of circulatory shock and hemodynamic instability, careful monitoring of heart function is essential to prevent further tissue hypoperfusion and subsequent organ failure. *ShockOmics* focuses on acute heart failure due to shock, and will explore the presence of biomarkers, which could be related (but not limited) to a cascade of pathogenic phenomena, whose onset is potentially associated to the role of the intestine and of the endocrine glands as a source of powerful mediators for tissue injury [26, 35]. *ShockOmics* aims at investigating the molecular triggers of AHF associated with shock and to identify inflammatory mediators and markers which are activated after an initial insult, with a particular emphasis on the role of uncontrolled proteolytic activity as a major cause of severe tissue injury. To achieve this goal, a systematic analysis of expression levels of transcripts, genes and their protein products, and of peptides generated by proteolysis will be carried out on blood samples obtained from ICU patients hospitalized. Based on the preliminary identification of candidate biomarkers of shock-induced AHF, animal experiments and in vitro studies will further validate the initial hypotheses on the fundamental mechanisms and on the biomarkers of the disease. This approach, besides focusing on new biomarkers of the disease, will aim to define new targets for therapy, in order to overcome the shortcomings of current therapies for circulatory shock. The final outcome of *ShockOmics* will be a multiscale integration of the information from different scales of investigation, from gene expression, to protein synthesis and metabolite expression, to organ specific injury in the heart and hemodynamic patterns characterizing the alteration of CV function in shock. In this framework, an important aspect is the interpretation of  the patho-physiological changes in system level variables, i.e. CV measurements, which are routinely available in emergency departments, ICUs and operating rooms, in function of the fundamental processes of disease.

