### Sample size

The sample size was computed taking into consideration the following assumptions:*ShockOmics* is an exploratory observational study aimed at testing new hypotheses on the molecular mechanisms of shock and consequent secondary organ failure, particularly AHF. Such hypotheses will be further explored and validated in animal models.Incidence of AHF in the population is low (average estimate 1.3 cases/1,000 subjects, increasing with age up to 11.6/1,000 in those aged 85 years and over) [37, 38]. Conversely, MOF and specifically AHF are a frequent and often lethal complication in shock patients. Shock increases re-hospitalization rates, organ failure and associated mortality even after ICU discharge [39]. Therefore, we expect to observe the activation of inflammatory factors and pathogens because of the local and systemic ischemia/reperfusion episodes occurring in shock, with an increased risk of AHF.Based on experimental and preclinical studies, we expect to test the occurrence of uncontrolled proteolytic activity, caused by serine proteases, metalloproteinases and other enzymes.

The sample size of *n* = 90 patients was calculated considering as outcome a quantitative measurement of cardiac function (i.e. cardiac output), and the following parameters: a) an Effect Size (f^2^) of 0.205 (for a strength of association equal to R^2^ 0.17); b) α type I error probability equal to 0.05; c) power = 81 %, using a multiple linear regression; d) 10 predictors tested in the model and giving the effect size.

If the strength of association (R^2^) for the selected set of predictors is equal to 0.20, the Effect Size (f^2^) would increase to 0.25, giving to the study a Power of 89 %, while for models with R2 higher than 0.24 the Power obtained would be higher than 95 %.

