The analyses of the blood samples and hemodynamic measurements will entail both analyses of the total sample (*n* = 90), which will allow the identification of common predictors across different types of shock, and of the subgroups of the different types of shock, which will allow to identify specificities associated to the disease etiology. A minimum sample size of *n* = 30 patients is needed per each subgroup in order to identify a set of predictors producing an Effect Size equal to 0.43 (for a strength of association equal to R^2^ 0.30), testing up to 3 predictors, with a Power of 80 %, and type I error α equal to 0.05. A maximum sample size of *n* = 60 patients will enable to identify a set of predictors producing an Effect Size equal to 0.25 (for a strength of association equal to R^2^ 0.20), testing up to 6 predictors with a Power of 80 %, and type I error α equal to 0.05.

In the specific case of hemorrhagic shock not determined by pre-existing pathologies (e.g., trauma patients), we expect the risk factors of low perfusion (i.e., reduced cardiac output) in these patients to be strictly related to shock. HS patients will be considered as reference shock population.

We will use data from septic patients and patients with acute heart disease not in shock together with septic shock and cardiogenic shock patients to conduct logistic regression analysis. Each subgroup analysis will be run on minimum of 40 subjects, allowing to identify single predictors with an Odds Ratio of 2.85 on a binary response variable defined as “shock onset”, with a Power of 83 % and type I error α equal to 0.05.

The sample size was estimated using G*Power 3 Calculator. We estimate that each ICU will recruit *n* = 50 patients in order to reach the above mentioned sample size, considering a drop out rate of ~40 %.

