### Clinical endpoints

The clinical endpoints that will be used to evaluate shock progression are:AHF assessed by a pool of measurements/estimates of cardiac function, including cardiac output, filling pressures, inotropic drugs requirements, left and right ventricles function estimated by echocardiography. AHF will be at evaluated at Time 1, 2, 3Mechanical ventilation free days or organ support -daysICU survivalOutcome at discharge from the ICU (objective: dead or alive, morbidities; subjective)Outcome at discharge from the hospital (objective: dead or alive, morbidities; subjective)

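### Eligibility and the heart-failure endpoint do not separate chronic from new cardiac dysfunction, so in the septic group (n = 60) old dysfunction can be counted as shock-induced acute heart failure.

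*Protocol article*

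**What the plan says.** The Background of the Protocol article states the target: the study "focuses on acute heart failure due to shock".

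Inclusion and exclusion criteria removes "Patients with pre-existing end stage renal disease needing renal replacement therapy", while allowing hemofiltration begun from the day of admission. It also removes Child-Pugh C cirrhosis and acute liver failure. The only cardiac exclusion is cardiac surgery in the previous ten days. The Abstract's shorter list likewise has no entry for chronic heart failure or known ventricular dysfunction.

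Clinical endpoints describes "AHF assessed by a pool of measurements/estimates of cardiac function, including cardiac output, filling pressures, inotropic drugs requirements" and echocardiographic function of both ventricles, evaluated at T1, T2 and T3. Sample size rests on "considering as outcome a quantitative measurement of cardiac function (i.e. cardiac output").

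The two -omics shock groups are defined differently. "Septic shock is defined as sepsis-induced hypotension" that persists despite fluids, with no condition on cardiac history. Cardiogenic shock must arise "because of ventricular failure due to acute cardiac conditions, such as acute myocardial infarction (AMI) or prolonged arrhythmias (PA").

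Clinical data collection lists comorbidities among the recorded items.

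**The concern.** The criteria distinguish old from new failure for the kidney but not for the heart, the organ under study. A septic patient with long-standing ventricular dysfunction can enter, can show poor cardiac measures at T1, and is not distinguished from a patient whose heart failed because of shock.

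This matters most in the septic group. In cardiogenic shock the heart is the cause by definition, and hemorrhagic patients have no -omics. The 60 septic patients are therefore the only -omics group in which heart failure as a consequence of shock can be separated from a primary cardiac cause. If chronic dysfunction is mixed in, molecules that mark chronic heart failure, its age profile or its drug treatment could be reported as markers of shock-induced AHF. None of the control groups (healthy donors, sepsis without shock, infarction or arrhythmia without shock) represents chronic heart failure, so they do not isolate that signature.

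**Working it through.** **1. Does any stated rule separate old from new dysfunction in septic patients?**

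| Place in the Protocol article | Content | Separates them? |
|---|---|---|
| Inclusion and exclusion criteria; Abstract | Only cardiac entry is recent cardiac surgery | No |
| Septic shock | Hypotension persisting after fluids | No |
| Cardiogenic shock | Acute cardiac cause required | Other group only |
| Clinical endpoints | Pool of cardiac measures at T1, T2, T3; no new-onset condition | No |
| Hemodynamic monitoring | Echocardiography on admission and later days | Before shock only if shock is diagnosed after admission; no rule uses it |
| Timeline; Biological samples | Blood sample at about day 100 in survivors | No cardiac assessment is stated for that visit |
| Clinical data collection | Comorbidities recorded | Supplies the data, not a rule |

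**2. The plan's own figures.** These are not in dispute. For the overall F test in multiple regression, with p predictors, the degrees of freedom are p and n − p − 1 and the noncentrality is f² × n.
- Total sample: n = 90, p = 10, f² = 0.205, noncentrality 0.205 × 90 = 18.45, df 10 and 79. Power is 80.7 % (stated 81 %).
- Septic group: n = 60, p = 6, f² = 0.25, noncentrality 0.25 × 60 = 15, df 6 and 53. Power is 79.0 % (stated 80 %).

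**3. How large could the mixing be?** The documents give no prevalence, so every input here is an assumption: 10 % or 25 % of the 60 septic patients have chronic dysfunction, and 40 % of the others develop new AHF.
- Chronic patients: 60 × 0.10 = 6, or 60 × 0.25 = 15.
- New AHF among the rest: 54 × 0.4 = 21.6, or 45 × 0.4 = 18.

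| Further assumption | 10 % chronic | 25 % chronic |
|---|---|---|
| All chronic patients count as AHF, none with an acute component | 6 / 27.6 = 22 % | 15 / 33 = 45 % |
| All count, but 40 % of them also have acute failure | 3.6 / 27.6 = 13 % | 9 / 33 = 27 % |
| Only half count as AHF, none with an acute component | 3 / 24.6 = 12 % | 7.5 / 25.5 = 29 % |

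The entries are the share of septic AHF that is wholly pre-existing.

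**4. What does each remedy cost in power?** Septic model, 6 predictors tested, f² held at 0.25.
- All 60 kept, flag added as a covariate: df 6 and 52, power 78.9 %.
- Flagged patients dropped, n = 54: noncentrality 13.5, df 6 and 47, power 73 %.
- Flagged patients dropped, n = 45: noncentrality 11.25, df 6 and 38, power 62 %.

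**The case against.** The strongest reply is that this belongs to the analysis plan. The article condenses a fuller protocol, comorbidities are collected, and how they enter the models is commonly settled in a document that is not shown. That stands as far as covariate adjustment goes. It does not cover eligibility or the endpoint description, both of which the article states and neither of which separates chronic from new dysfunction.

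Partial safeguards also exist. Repeated assessment at T1 to T3 permits within-patient change to be studied. The admission echocardiogram can precede shock in patients diagnosed later. The day-100 sample might show which molecules persist. No stated rule uses any of them to classify AHF, and the first two give no pre-shock reference for patients admitted already in shock.

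Three stronger readings are tempting but unsupported:
- A reader might infer that a septic patient with a chronically low ejection fraction is certain to be scored as AHF. Clinical endpoints gives no cut-off or scoring rule, and the 35 % ejection-fraction threshold is listed for the cardiogenic group. The documents support only that such a patient can be counted.
- A reader might take "In the specific case of hemorrhagic shock not determined by pre-existing pathologies (e.g., trauma patients), we expect the risk factors of low perfusion" as an admission that only hemorrhagic patients are free of this problem. The sentence does not say only. Its qualifier concerns the origin of the hemorrhage and does not mention chronic heart failure.
- A reader might infer that such patients should have been excluded. The documents do not require that, and dropping them carries the power cost shown above.

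**Conclusion.** The concern holds in a limited form. Eligibility leaves pre-existing heart failure unaddressed, and AHF and cardiac output are assessed after shock diagnosis without a new-onset condition. In the septic group, chronic dysfunction can therefore be attributed to shock and confound the biomarker associations. In the cardiogenic group the acute-cause wording narrows the problem, though it does not rule out acute-on-chronic disease.

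The size cannot be determined from the documents. The 12 % to 45 % range illustrates what the assumed inputs imply; it is not an estimate. It also treats AHF as a yes/no status, whereas the outcome used for sizing is quantitative cardiac output. The sample-size calculations are unaffected. This is a worthwhile, low-cost improvement to an exploratory study.

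**What to change.** - From the recorded comorbidities, derive one flag: known chronic heart failure or a previously documented reduced ejection fraction.
- Keep all septic patients in the main AHF and cardiac-output biomarker models, with the flag as a covariate.
- Report a sensitivity analysis without flagged patients, in which AHF means dysfunction not known before shock. Give the number flagged.

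No new exclusion or procedure is needed, which suits a study with 64 of 90 patients already recruited. The cost is one derived variable and one model term. The drop from 79.0 % to 78.9 % assumes that the predictors' effect size stays at 0.25 after adjustment; it would be larger if the flag shares explained variance with the biomarkers. The sensitivity analysis has less power: 73 % if 6 patients are flagged and 62 % if 15 are. Prior dysfunction that was never documented is missed, so some confounding will remain and should be stated as a limitation.

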### Timeline of data collection

Time 0 (T0): admission to the ICU with diagnosis of shock or time of shock diagnosis in patients initially admitted without shock symptoms (see inclusion/exclusion criteria above);Time 1 (T1): time at which the first blood sample for analysis is collected, within 16 h after T0. This time point is considered representative of acute shock before the therapy has taken effect, when shock has already activated the main patho-physiological cascades of inflammation and disease;Time 2 (T2): time at which the first blood sample for analysis is collected, at 48 h after T0. At this time point, the treatment has been administered for a long enough amount of time to evaluate its effects on the early molecular markers of disease;Time 3 (T3): time at which the third blood sample for analysis is collected, on day 7 of the ICU stay of the patient or before discharge from the ICU in case of shorter stays or before discontinuing therapy (death). At this time point, the activated molecular pathways and the relevant system level consequences are assumed to have reached a steady state condition;Time 4 (T4): follow up (FU) on ~ day 100 from Time 0. A blood sample will be collected in survivors who will not be re-hospitalized for the consequences of shock during the time between T3 and T4.

The time course of data collection for the protocol is shown in Fig. 1.

**Fig. 1 Fig1:**
[figure not shown]
Time course of the monitoring of a patient enrolled in the *ShockOmics* study (hemodynamic data acquisition and blood samples). The hemodynamic data are collected daily during the observation window (up from time 0 on day 1 up to day 7). The total number of blood samples is 3: the first sample is collected at T1, the second at T2, and the third at T3, which can occur on any day between day 4 and day 7 (T3 occurring on day 7 in case of ICU stay longer than 7 days or on day 4–6 in case of early discharge or death)

### Clinical endpoints

The clinical endpoints that will be used to evaluate shock progression are:AHF assessed by a pool of measurements/estimates of cardiac function, including cardiac output, filling pressures, inotropic drugs requirements, left and right ventricles function estimated by echocardiography. AHF will be at evaluated at Time 1, 2, 3Mechanical ventilation free days or organ support -daysICU survivalOutcome at discharge from the ICU (objective: dead or alive, morbidities; subjective)Outcome at discharge from the hospital (objective: dead or alive, morbidities; subjective)

### Clinical data collection

The following anamnestic and clinical data will be recorded daily from T1 until T3:Laboratory data from urine and blood samplesComorbiditiesSeverity scores (SOFA and APACHE II scores)Time from onset of symptoms to shock diagnosisTime from ICU/ER admission to shock diagnosisBiochemical parameters, e.g. lactate levels, pH, etc.Therapy (drugs, fluids, etc.), temperature, urine output, stool production, bowel sound, abdominal fullness, appetite, food and fluid consumption or fasting, nausea and vomitingCardiorespiratory assistance (mechanical ventilation, ECMO, intra-aortic balloon pump, etc.)Assessment of organ failure, and in particular heart failureCognitive assessment (encephalopathy) - by SAS, RASS and CAM-ICU scaleFor the patients not discharged from the ICU on day 7, the clinical data will be recorded on day: 10/15/22/30 and every 15 days until discharge from the ICU

### Biological samples

Urine and blood samples will be collected at the times T1, T2, and T3. The typical management of shock patients in ICU requires arterial, venous and urinary catheterization. These accesses are routinely used for drug/fluid administration and will also be used for the collection of the samples for analysis.

The ICU staff will contact survivors in order to schedule a follow-up visit on day 100 (T4, Recovery), during which a blood sample will be withdrawn for analysis.

The collection and analysis of urine will permit to evaluate standard biochemical parameters, routinely required to integrate the information from blood analysis, such as for instance kidney function, liver function, medullary function, etc.

### Hemodynamic monitoring

The hemodynamic data will be downloaded from the bedside ICU monitor on a laptop computer by means of dedicated software. Details on the implementation of the solutions to the technical issues of downloading signals from the monitors and on the acquisition protocol are addressed in the Discussion section.

The continuous waveforms, which will be routinely accessible, include:ECGABP, via an arterial catheter inserted in the femoral or radial arteryCVP, in patients with a central venous line with a pressure transducerPPGRespiratory signals: bio-impedance or thoracic beltContinuous SpO2

Further, continuous and non-continuous measurements and estimates, which will be available intermittently, will include:Continuous measurements of PAP, PAOP, and estimates of CO via thermodilution, by means of a pulmonary artery catheter, when in useStroke volume, CO, global end diastolic volume, extravascular lung water from trans-pulmonary thermodilution (PiCCO ® [Pulsion Medical System]) when in useTrans-thoracic or trans-oesophageal echocardiographic assessment on admission, on Day1, Day2, Day3, Day7/Discharge/DeathVentilation parameters (settings of mechanical ventilation if applicable; including pressure, tidal volume, static compliance, etc.) on Day1, Day2, Day3, Day7/Discharge/DeathCentral or mixed venous oxygen saturation and artero-venous pCO_2_ difference on Day1, Day3, Day7/Discharge/Death.

